### 2.4.5.2. Independent Variables (Primary Explanatory Variable, Process Measures, and Covariates)

**Choosing Wisely Participation Status.** We will use several methods to identify and confirm participation status at the 3-4 month time point after the initiative starts. If the information is reported to VACO,

we will obtain these data from the leadership of the VA's initiative (see [name] support letter). We will contact key individuals in each VISN (Chief Medical Officer) and all facilities (Chief of Staff, Chief of Ambulatory Care, and others if necessary) by email with phone call follow-up if necessary. We will also survey by email the clinical pharmacy specialists at each facility. This approach will be used solely to determine participant status and not to obtain details regarding specific actions within a facility.

**Commitment to Quality at Baseline.** We will use overall quality of care as a surrogate and use the quality quintile (Gold Star rating) from first qtr FY2014 provided by Strategic Analytics for Improvement and Learning (SAIL) of the Office of Informatics and Analytics. These ratings are calculated quarterly and are a composite of a broad series of measures of all aspects of quality.

**Teaching Intensity.** Teaching status has been associated with quality of care. Since the majority of VA hospitals are affiliated with medical schools, we will use a measure of teaching intensity. Teaching intensity =  $\sum (\# \text{ family practice trainee slots}) + (\# \text{ internal medicine trainee slots}) + (\# \text{ internal medicine subspecialty slots})$ . These are the trainees who would be involved in primary care and specialty consultation related to diabetes. In 2013 this value had a mean $\pm$ 1SD of 39 $\pm$ 33 with a range of 0-125. Of note, each trainee slot represents ~4 trainees rotating part time at the VA.

**Safety Culture.** We will use results from the National Center for Patient Safety Culture Survey, which is conducted every 3-5 years, the latest occurring in 2011. The survey which we plan to use in the analyses will occur after the initiative is underway. We will calculate a score based on results of the domains of "Overall Perceptions of Safety," "Perceptions of Patient Safety at your Facility," and "Senior Management Awareness/Actions in Promoting Safety." (See questions in the Appendix.) Scores will be divided into quintiles.

**Comorbidities.** Using ICD 9CM codes we will create indicators of advanced complications of diabetes, limited life expectancy, cardiovascular or ischemic vascular disease, and major medical and mental health conditions that would impact benefit or risk of tight control based upon previously published taxonomies.

**Demographic Variables.** We have developed algorithms to process multiple entries of patient data over time and from a variety of sources to optimize the demographic information available for research. Sources include many years of VA inpatient and outpatient data with multiple fields and Medicare data. Consequently, we have nearly complete and largely confirmed assignments for most variables, including age and sex. Because of limitations in data concerning race/ethnicity, we will not assess this variable.

**2.4.6. Identification of High and Low Performers.** High and low performers will be identified based on changes in facility overtreatment rates pre- and post-initiative (rather than on absolute values). Those with the greatest (high performers) and least reduction (low performers) in overtreatment rates will be selected. To

minimize issues related to regression to the mean, we will focus on facilities that were mid-performing at baseline (2nd and 3rd quartiles). See Fig. 4. Among the middle-performing facilities at baseline, we will select those facilities with the greatest reduction in overtreatment rates (high performers) and those with the least reduction (low performers). We will also select from among the highest performers at baseline who improved at all as well as some low performers at baseline who stayed low. It is impossible to know how many facilities will fall into these categories; but we are anticipating approximately 5-10 in each group (total n~30). Aim 3 does not include hypothesis testing, but is instead looking for identifying patterns of provider and facility characteristics associated with performance status (high vs. low). Our methods of analyses (matrix and qualitative comparative analysis) allow for a small sample size. Performance status will be determined independently of Choosing Wisely participation status; selected sites will likely include those facilities choosing the hypoglycemia initiative alone or both hypoglycemia and low back pain initiatives. If entire VISNs participate

[figure not shown]

in the initiative, we will seek positive deviants, i.e., facilities which are statistically higher performers than other facilities in the same VISN. Positive deviants may provide special insights into successful implementation

strategies. We will identify them as we have done previously using a statistical approach recommended by the National Committee of Quality Assurance. In order to characterize these sites further as to their performance over time, we will also examine facility rates at baseline and at 2 years following the start of the intervention. Rates at 2 years will provide information about sustainability of improvement. We note that this study sample is a dynamic cohort since new members are added as they meet the study criteria.

**2.4.7. Quantitative Data Sources and Collection.** We will obtain VHA data from Corporate Data Warehouse (CDW), a national repository of data, and other VA files. The goal at VA has been to transition most VA data to reside on CDW servers. We will include files containing patient characteristics, outpatient and inpatient encounters, diagnosis and procedure codes, pharmacy/prescription information, and laboratory (A1c and serum creatinine) values from 2012 to 2016. We will use CMS data (when available), which includes Medicare (for outpatient and inpatient encounters, diagnosis and procedure codes, eligibility status) and Medicaid (for additional pharmacy/prescription information), as we have done previously. Data for commitment to quality, safety culture, and teaching intensity are described above (2.4.5.2). Specific data files are described below:

**Patient Medical Encounter Data** include file records for all VA inpatient and long-term stays and all outpatient visits, with information on patient characteristics, eligibility, type of care, and multiple codes for diagnoses (ICD-9-CM codes) and procedures (ICD-9-E or CPT4 codes). They are VHA Medical ASA (MEDSAS) datasets.

**VA Laboratory Data** are recorded at each site for all tests performed and subsets are extracted to national databases. We recognize that not all patients in our study will have results available from laboratory tests. In our prior work, we have found that, based on CPT codes, most VHA patients with diabetes receive the majority of their outpatient laboratory tests in VA clinics, and have regular measures of A1C and creatinine.

**Pharmacy Records** will be obtained from the Pharmacy Benefits Management Strategic Health Group (PBM). This national VA prescription database includes information on specific medications, including dates, duration, dose, and physician instructions. The PBM uses a verification process to assure data accuracy and completeness. Use of non-VA pharmacy services by VA patients is not included in PBM. To address this potential limitation, we will include data from Medicare Part D and Medicaid prescription records (if available). We note that such information may not be available for the entire study period due to time lags.

**2.4.8. Quantitative Data Statistical Analyses.** We will begin all analyses with inspection of frequency distributions and bivariate analyses of means (t-tests and ANOVAs) and proportions (Chi-square tests) among subgroups defined by our independent variables, and will use graphical methods for exploratory data analysis. We will enter variables into statistical models according to our conceptual framework and hypotheses. Cells in the cross tables with 0 or small numbers will be collapsed with other cells. In handling variables with missing data, the primary analyses will be restricted to those with values (complete case analysis); alternatively, patients with unknown values for a variable will be grouped into a subcategory to be included in the statistical models. Our analyses need to account for the possibility that observations may not be completely independent due to individuals nested within a VA facility, and VA facilities nested within a VISN. We will use hierarchical modeling (also termed multi-level models/mixed effects models/random-effects models) for the analysis of correlated data to address the issue of possible underestimation of variance for regression coefficient estimates under conventional regression models. In the statistical models, facilities and VISNs will be considered as random effects. Other than the primary exposure variable specified in each hypothesis, independent variables will also be included in the statistical models as control variables.

**Aim 1.** To assess the *overall* impact, both intended and unintended, of the Choosing Wisely Initiative. All analyses will be conducted for various subgroups of high risk patients. Due to the nature of the outcome variable in the quantitative aims (Aims 1 and 2), the primary statistical technique for these two aims will be logistic regression. The “logit” (i.e., log of odds) of the presence of an event is regressed on a list of independent variables. We will use odds ratios (=exponentiation of the estimated regression coefficients) and their confidence intervals for the hypothesis testing. An odds ratio larger (smaller) than 1 with a 95% confidence interval not containing 1 indicates a higher (lower) likelihood of the occurrence of an event for the group in comparison relative to the reference group in an independent variable. In Aim 1 we will use multinomial logistic regressions to model the outcome variable, a polytomous variable. In the models the polytomous variable is treated as a nominal variable and a value in the variable is treated as the reference group; separate logistic regression models for the probabilities of non-reference groups against the reference group are constructed and estimated simultaneously. This approach is more efficient than separately conducting two logistic regression models (i.e., the overtreated versus those in moderate control and the

undertreated versus those in moderate control). The primary exposure variable in both H1.1 and H1.2 is the group indicator variable. Along with the previously listed independent variables, a patient's glycemic control status in the pre-initiation period will also be included in the models as a control variable. We will assess both the implementation and sustainability phases of the initiative.

**Aim 2.** To assess the impact of facility commitment to quality, teaching intensity, and safety culture on patients' likelihood of overtreatment. We will use a similar modeling strategy to Aim1 for this aim but employ binary logistic regression models, because the hypotheses focus on overtreatment (a binary variable: overtreatment versus moderate control). We will construct separate models for each of H2.1a, H2.1b, and H2.1c. We will also evaluate the associations among the three primary exposures variables in the hypotheses, and construct a statistical model including all three variables and compare with the separate models.

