
**Aim 1.** To assess the overall impact, both intended and unintended, of the Choosing Wisely Initiative.

H1.1. Patients treated in facilities that focus on hypoglycemia risk reduction will have a lower likelihood of overtreatment compared to those treated in other facilities.

H1.2. Patients treated in facilities that focus on hypoglycemia risk reduction will have the same likelihood of undertreatment compared to those treated in other facilities.

**Aim 2.** To assess the impact of commitment to quality, teaching intensity, and safety culture on patients' likelihood of overtreatment.

H 2.1a. Patients treated in facilities with higher levels of commitment to quality are less likely to be overtreated compared to those in facilities with lower levels of facility commitment to quality.

H2.1b. Patients treated in facilities with higher level of teaching intensity are less likely to be overtreated compared to those in facilities with lower level of teaching intensity.

H2.1c. Patients treated in facilities with higher level of safety culture are less likely to be overtreated compared to those in facilities with lower level of teaching intensity.

**Aim 3.** To identify configurations of the implementation strategy (Choosing Wisely toolkit), provider characteristics and organizational level factors that are associated with successful reduction of overtreatment rates by comparing high and low performers. Our sample size will be insufficient for formal hypothesis testing, but we will examine the following research questions using matrix and qualitative comparative analyses:

RQ3.1. Which configurations of the Choosing Wisely toolkit are associated with greater reduction in overtreatment rates?

RQ3.2. Which configurations of provider characteristics and organizational factors are associated with greater reduction in overtreatment rates?

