**2.4.3. Study Populations.** The population for Aims 1 and 2 will be VHA clinic Veteran users with diabetes receiving insulin and/or sulfonylurea treatment in the time period 4/1/14 to 3/31/2015 (the initiative start date being 4/1/2014). A Veteran is determined to have diabetes if one has VHA service use in the year and has two or more visits with diabetes ICD-9-CM codes (250.XX) from inpatient or outpatient (face-to-face) care over a two year period or has prescriptions for diabetes medication in the year. Aims 1 and 2 will utilize longitudinal data from Veterans with diabetes who have at least 1 A1c value. For our primary outcome measure of overtreatment (see below), we will include patients having at least one of the following additional criteria: age >75 years, last serum creatinine  $\geq 2.0$  mg/dl, or an ICD-9-CM diagnosis of cognitive impairment or dementia in ambulatory care. From a population health perspective, individuals 75 years of age and older have limited life expectancy and an increased co-morbid illness burden, and thus have decreased life-time benefit and increased risk from intensive glycemic control. Impaired renal function affects metabolism of oral hypoglycemic agents and insulin. In the ACCORD trial, subjects with serum creatinine levels between 1.0 and 1.3 mg/dl had greater risk of serious hypoglycemia than those with normal creatinine levels (<1.0 mg/dl); subjects with creatinine >1.3 mg/dl had even greater risk. To be conservative, we have restricted our measure to even worse renal function. As a sensitivity analysis, we will evaluate patients with age greater than 70 years or a serum creatinine > 1.7 mg/dl. Cognitive impairment may adversely affect patients' ability to self-manage their diabetes and is associated with increased risk of serious hypoglycemia in both the control and intensive treatment arms of the ACCORD trial.

**2.4.4. Power Analysis.** Power calculation in hierarchical/multi-level models is not straightforward and there are no established norms. The power calculation for such models needs to consider sample sizes in all levels involved. For a two-level model, a rule of 30 groups and 30 subjects per group is usually recommended to ensure sufficient power for fixed effects. Using Optimal Design® software, we conducted power analyses for detecting

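### Safety culture is to be surveyed after the initiative starts, yet it is a control variable in Aim 1 and the exposure in H2.1c; the existing 2011 survey should be used instead

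*Protocol*

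**What the plan says.** **Safety culture.** Section 2.4.5.2 takes the score from a national patient safety culture survey, "which is conducted every 3-5 years, the latest occurring in 2011". It does not use the 2011 round: "The survey which we plan to use in the analyses will occur after the initiative is underway". No date and no reason are given. The score combines three domains, one of which is "Senior Management Awareness/Actions in Promoting Safety", and is divided into quintiles.

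**Outcome window.** Section 2.4.3 defines the population for Aims 1 and 2 by treatment "in the time period 4/1/14 to 3/31/2015 (the initiative start date being 4/1/2014"). Section 2.4.5.1 classifies each patient by the last A1c in the period.

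**Companion exposure.** The commitment-to-quality variable is labelled as a baseline measure, and the plan will "use the quality quintile (Gold Star rating) from first qtr FY2014".

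**Adjustment rule.** Section 2.4.8 says that, apart from the primary exposure of each hypothesis, "independent variables will also be included in the statistical models as control variables". Its Aim 1 paragraph repeats that the independent variables already listed enter those models, together with pre-initiative glycemic status. Its Aim 2 paragraph adds a joint model containing all three facility exposures.

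**Teaching intensity.** "Since the majority of VA hospitals are affiliated with medical schools, we will use a measure of teaching intensity". The measure is the sum of three kinds of trainee slots; the 2013 values had mean 39, SD 33 and range 0 to 125.

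**H2.1c (section 2).** "facilities with higher level of safety culture are less likely to be overtreated compared to those in facilities with lower level of teaching intensity".

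**The concern.** A control variable in a comparison of participating with non-participating facilities should not itself be open to change by participation. Here it may be. A leadership-backed medication-safety campaign could plausibly alter how staff rate management action on safety, and the survey is taken once the campaign is running. If so, the score lies on the path from participation to overtreatment, and holding it fixed removes part of the effect that Aim 1 is meant to estimate. If some unrecorded facility trait, such as leadership engagement, drives both the later answers and the prescribing, adjusting for the score can also distort the comparison in a direction that is not known in advance.

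Where the distortion is attenuation, it would work against H1.1, which expects a difference, and in favour of H1.2, which expects none.

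For H2.1c the issue is order in time. Aim 2 is worded as an impact of safety culture on overtreatment, but the score may be collected after some or all of the A1c values it is meant to explain.

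**Working it through.** The protocol states no figure on this point that could be reproduced. The check sets dates and model terms side by side.

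**Step 1: when the survey falls.** Last survey 2011, cycle 3 to 5 years (section 2.4.5.2): 2011 + 3 = 2014 and 2011 + 5 = 2016. The text also places it after the start on 1 April 2014. The outcome window closes on 31 March 2015.

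| Survey taken | Relative to participation | Relative to the last A1c in the window |
|---|---|---|
| Early in the window | After the start | Before it for many patients |
| Late in the window | After the start | After it for many patients |
| After 31 March 2015 | After the start | After it for all patients |

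The middle column never changes, so the Aim 1 problem arises under every permitted date. The right-hand column does change, so the severity for H2.1c depends on a date that the protocol does not give.

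**Step 2: which models carry the score.** By the adjustment rule and the Aim 1 paragraph of section 2.4.8, it is a control in the models for H1.1 and H1.2. By the Aim 2 paragraph, it is the exposure for H2.1c and one of three exposures in the joint model, where it stands beside a quality rating fixed at baseline.

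**Step 3: what adjustment does.** Let a be the effect of participation on the score and b the effect of the score on the log-odds of overtreatment. As an approximation (odds ratios are not exactly collapsible), adjusting for the score removes about a × b from the participation coefficient. The protocol gives neither a nor b, so the bias cannot be sized. It is zero if a = 0 or b = 0, apart from any distortion through a shared unrecorded cause. The 2011 score cannot have been changed by an initiative that begins in 2014, so a = 0 for it by construction, while it still controls for prior differences between facilities.

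**Step 4: age of the alternative.** 2014 − 2011 = about 3 years at the start.

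**Step 5: teaching intensity.** The measure has no denominator. High-risk patients per facility run from 300 to 7,000 (section 2.4.4), and 7,000/300 = 23.3-fold. The covariates in sections 2.4.5.2 and 2.4.8 include no size or complexity variable; complexity appears only as a criterion for choosing site visits (section 2.4.9). The facility and VISN random effects handle correlation within clusters and do not adjust for size.

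**The case against.** **The study is observational and says so.** Section 2.4 promises cautious causal inference and describes Aim 2 as assessing associations. That stands as far as it goes: a reader might infer that H2.1b and H2.1c cannot be tested at all, and the protocol does not support this. Both are between-facility comparisons and remain estimable. What is weakened is the impact or directional reading. Cautious language does not change when a variable is measured.

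**The covariate set could be settled in the SAP.** Section 2.4.8 also says that variables will enter according to the conceptual framework. But the protocol itself fixes both the survey timing and the rule that the listed variables are controls. Followed as written, it adjusts Aim 1 for a score taken after the start.

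**The effect on the score may be small.** The initiative would have to move a facility's quintile on a three-domain, facility-wide score. That is fair, and nothing in the protocol shows that it would. Participation status and prior glycemic status are also controls in the Aim 2 models under the general rule, which closes part of the path for H2.1c. Neither helps Aim 1, where participation is the exposure.

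**The 2011 score is old.** This is true. It is a reason to keep the later survey as a sensitivity analysis for H2.1c.

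**Teaching intensity.** The formula is defined and the choice of trainee types is explained. A reader might infer that the slot count follows facility size and that H2.1b is therefore confounded. The protocol reports no link between slots and size, or between size and overtreatment, and confounding needs both. One can compute that the mean of 39 slots is 39/300 = 13 per 100 high-risk patients at the smallest facility and 39/7,000 = 0.56 per 100 at the largest. That assigns the same count to two hypothetical facilities. It shows only that a count is not a density and does not measure bias.

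**Conclusion.** The main point holds as a cheap improvement. The plan uses a safety-culture score collected after the initiative starts, although a 2011 score exists and the quality exposure is taken at baseline. In Aim 1 the later score may remove or distort part of the participation effect; in H2.1c temporal order is not secured. Both statements are about possible bias. They rest on the assumption that the campaign can move safety-culture answers, or that something unrecorded drives both those answers and prescribing. The size cannot be computed, and reverse causation is not established because the survey date is unknown.

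The teaching-intensity point is secondary: confounding by facility size is plausible but undocumented, and merits a sensitivity analysis only. The H2.1c comparator is a clerical slip, since the Aim 2 objective and section 2.4.8 make the intended exposure clear.

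**What to change.** 1. **Aim 1:** make the 2011 survey the only safety-culture covariate, and state that these models will not adjust for the later score.
2. **H2.1c:** use the 2011 score as the baseline exposure. Report the later survey as a sensitivity analysis, giving its date relative to the start and to the outcome window. Use the 2011 score in the joint Aim 2 model as well.
3. **H2.1b:** add a sensitivity analysis with log facility patient count in the model, and list that variable among the covariates.
4. **H2.1c wording:** change the comparator to facilities with a lower level of safety culture.

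The cost is a few sentences and one derived variable; no new data collection is needed. The downside is that the 2011 scores are about three years old at the start and may describe the facilities of 2014 less well, which the sensitivity analysis in item 2 is there to show.

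### Aim 1 is written to adjust the participation effect for a safety culture score surveyed after the initiative has begun, and the same covariate rule contradicts the separate-versus-joint model comparison in Aim 2

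*Protocol*

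**What the plan says.** Protocol section 2.4.5.2, headed "Independent Variables (Primary Explanatory Variable, Process Measures, and Covariates)", describes six items: Choosing Wisely participation status, commitment to quality, teaching intensity, safety culture, comorbidities and demographic variables. On safety culture it says: "The survey which we plan to use in the analyses will occur after the initiative is underway". The latest survey then available dates from 2011.

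Section 2.4.8 gives the general covariate rule: "Other than the primary exposure variable specified in each hypothesis, independent variables will also be included in the statistical models as control variables".

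The Aim 1 paragraph of 2.4.8 names the participation group as the primary exposure for H1.1 and H1.2, and then states: "Along with the previously listed independent variables, a patient's glycemic control status in the pre-initiation period will also be included in the models".

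The Aim 2 paragraph says: "We will use a similar modeling strategy to Aim1 for this aim but employ binary logistic regression models". It continues: "We will construct separate models for each of H2.1a, H2.1b, and H2.1c". It then plans to look at associations among the three traits and to "construct a statistical model including all three variables and compare with the separate models".

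**The concern.** There are two faults, and a third point that the text leaves open.

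**Aim 1.** A control variable should not be something that the exposure can alter. The safety culture score is surveyed after the start, and one of its three domains concerns what senior management knows and does about safety. The protocol presents reducing overtreatment as a medication safety effort. A facility that takes up the hypoglycemia topic could score higher because it took it up. Adjusting for the score could then remove part of the effect that H1.1 is meant to detect, and could distort the H1.2 comparison on undertreatment.

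**Aim 2.** If every listed variable other than the exposure under test is a control, each single-trait model already contains all three traits. Comparing it with the joint model would then show nothing. The general rule and the Aim 2 text cannot both be followed, and an analyst would have to choose between them, possibly after seeing results.

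**Participation in Aim 2.** No sentence says whether participation is left in or out of the H2.1a-c models. The two choices answer different questions: a total association of the trait with overtreatment, or an association net of participation.

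**Working it through.** The plan gives no figure to reproduce here. The check compares covariate sets and timing, with a small illustration for participation.

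**1. Listed variables and their timing (section 2.4.5.2)**

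| Variable | Timing |
|---|---|
| Participation status | confirmed 3-4 months after the start |
| Commitment to quality | first quarter FY2014, labelled baseline |
| Teaching intensity | 2013 values shown |
| Safety culture | survey held after the start |
| Comorbidities, demographics | patient level |

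**2. Aim 1 model.** The exposure is participation. The controls, from "Along with the previously listed independent variables", are quality, teaching, safety culture, comorbidities and demographics, plus pre-initiation glycemic status. Safety culture is the only facility-level control explicitly measured after the start.

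On a linear approximation, the part of the participation effect removed is a × b. Here a is the shift in the score caused by participation, and b is the change in overtreatment per unit of score. The documents give neither, so no size can be stated. If participation raises the score and a higher score goes with less overtreatment, the estimate moves toward no effect. If the score and overtreatment share unmeasured causes, conditioning on the score can move the estimate either way.

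**3. Aim 2 models under the literal rule**

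- H2.1a: quality + {participation, teaching, safety, comorbidities, demographics}
- H2.1b: teaching + {participation, quality, safety, comorbidities, demographics}
- H2.1c: safety + {participation, quality, teaching, comorbidities, demographics}
- Joint: {quality, teaching, safety} + {participation, comorbidities, demographics}

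All four are the same set. A simulated logistic example (400,000 records, no clustering, assumed effects) bears this out. The H2.1a, H2.1b and joint fits share one log-likelihood: -231486.29 when the assumed log odds ratio of quality on participation is 0.5, and -230285.44 when it is 1.0.

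**4. Aim 2 models under the specific Aim 2 text.** The comparison is informative only if each separate model omits the other two traits. Each then differs from the joint model by two variables. This reading conflicts with step 3.

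**5. Participation in Aim 2 (illustration only).** In the same simulation, quality acts on overtreatment solely through participation. Its odds ratio per SD is:

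| Assumed log odds ratio, quality on participation | Quality alone | Literal rule |
|---|---|---|
| 0.5 | 0.971 | 1.006 |
| 1.0 | 0.934 | 1.000 |

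On the percentage-point scale, the part removed = (participation gap between high- and low-trait facilities) × (participation effect). The effect is taken as 1.7 points (section 2.4.4: 0.290 - 0.273 = 0.017) or 4.6 points (smallest VISN 12 fall, same section). The gap of 20 to 40 percentage points is an assumption.

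- 0.20 × 1.7 = 0.34
- 0.40 × 1.7 = 0.68
- 0.20 × 4.6 = 0.92
- 0.40 × 4.6 = 1.84

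**The case against.** The strongest reply is that the conflict comes from reading one sentence too literally. The rule exempts the exposure named in each hypothesis. Taken collectively, that could exempt participation and all three traits, leaving only comorbidities and demographics as controls. The 2.4.5.2 heading itself separates explanatory variables from covariates. Section 2.4.8 also ties the entry of variables to the conceptual framework and hypotheses, and specific Aim 2 text would normally override a general sentence.

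For Aim 2 much of this stands. A reader might infer that the plan settles on identical separate and joint models. It does not: the Aim 2 paragraph implies that each separate model omits the other two traits. What remains is a contradiction to reconcile.

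For Aim 1 the reply fails. The Aim 1 paragraph carries in the listed independent variables without excepting safety culture. The framework sentence names no variable to leave out. Detailed covariate lists may well sit in a statistical analysis plan, but a control stated here and a conflict between two statements here are not missing detail.

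A second reply is that a score taken shortly after the start may mostly reflect long-standing culture, so adjusting for it could reduce confounding of a self-selected exposure. That is fair. It argues for a score from before the start, such as the 2011 one, which cannot have been affected by participation.

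A third reply concerns participation in Aim 2. The choice of topic may be made at VISN level, so a facility's traits need not drive it. The protocol states no total-effect target and disclaims establishing causality. All of this stands.

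**Conclusion.** The Aim 1 fault holds as written: a score measured after the start is a control for H1.1 and H1.2. Its effect on the estimate depends on how far participation shifts the score and how the score relates to overtreatment. Neither is given, so the bias is possible but cannot be sized. It is worth correcting because dropping the score costs almost nothing.

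The Aim 2 fault holds as a contradiction between the general covariate rule and the separate-versus-joint comparison.

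A reader might go further and infer that adjusting for participation wipes out the trait effects in H2.1a-c. The documents do not support that. A trait would look null only if its whole effect ran through participation; any direct effect would remain. The argument that participation lies on the path suits quality and probably teaching, which come before it. It does not suit H2.1c, where participation may precede the measured score and could confound it, so leaving it out could itself bias the result.

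The 0.3 to 1.8 point range is illustrative. The participation gap is assumed, the VISN 12 fall is not a comparison of participants with non-participants, and only the most extreme of the four combinations exceeds the plan's detectable difference of 1.7 points.

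**What to change.** 1. **Aim 1:** remove the post-start safety culture score from the control set. If adjustment for safety culture is wanted, use the 2011 survey score. The cost is an absent or older adjustment.
2. **Aim 2, traits:** amend the covariate rule in section 2.4.8 so that each of the H2.1a, H2.1b and H2.1c models excludes the other two traits. Keep the three-trait model as the comparison.
3. **Aim 2, participation:** state for each hypothesis whether participation is omitted (total association) or included (association net of participation), and report the other version as a sensitivity analysis. Do not omit it automatically for H2.1c.

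This takes a few sentences of protocol text. Items 2 and 3 need no new data. Item 1 needs none if the score is simply dropped; the 2011 option needs that survey's facility scores. The changes should be made before outcome data are examined, so that the choice between models is not made on results.
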